### Study registration information

This study has been registered at [clinicaltrials.gov](https://clinicaltrials.gov) (NCT04851457) and the China Clinical Trial Registry (ChiCTR 2100045661).

## IV. Study background

### 1. epidemiology

Stroke is a worldwide health problem, with an estimated 13.7 million new strokes and approximately 5.8 million deaths annually (<http://world-stroke.org/>), making stroke the second leading cause of death in the world [1]. In addition, there are currently more than 80 million stroke survivors worldwide, of whom an estimated 50% suffer from moderate to severe neurologic deficits [2], and a quarter require permanent assistance. Stroke has become the third leading cause of adult disability worldwide [3]. In China, the number of new stroke cases is more than 2 million annually. What's worse, the burden of stroke is predicted to rise further in the coming decades as a result of population aging and ongoing high prevalence and inadequate management of risk factors such as hypertension, which is recognized as a major global public health challenge[4].

Stroke can be classified into ischaemic stroke (occlusion of a blood vessel) or hemorrhagic stroke (bleeding into the brain), with the former making up about 70% of strokes[2]. Acute ischemic stroke (AIS) is a vascular accident caused by thrombosis or embolism that occludes a cerebral vessel supplying a specific region of the brain, resulting in ischemia and hypoxic necrosis of local brain tissue and corresponding neurological deficits. After an ischaemic stroke, there is a core area where damage to the brain is irreversible and an area of penumbra where the brain has lost function owing to decreased blood flow but is not irreversibly injured. Rapid reperfusion therapy aims to restore blood flow in the ischaemic penumbra and salvage neurons in the penumbra, returning them to normal function [5, 6]. Therefore, early recanalization therapy is of great significance in reducing post-stroke disability and has become the mainstay of AIS treatment.

In the past 20 years, intravenous use of recombinant tissue plasminogen activator (rt-PA) has become the main method to achieve vascular recanalization after ischemia [7,8].

However, due to the narrow therapeutic time window of rt-PA treatment, many contraindications to its use, and the low effectiveness of recanalization in the case of large artery occlusion, in addition to the risk of serious secondary bleeding [9], its clinical application has been limited to approximately 15% of patients with acute ischaemic stroke. In addition, arterial interventional therapy has demonstrated much higher efficacy in large artery occlusions [10]. A growing body evidence has shown that arterial interventional therapy can benefit some patients with ischemic stroke [11], and it has become the preferred treatment for patients with anterior circulation large vessel occlusion stroke within 24 hours, although screening with advanced imaging techniques is required to select patients who will benefit over this extended timeframe [12, 13]. However, arterial interventional therapy can cause endothelial injuries leading to local activation of platelet aggregation and subsequent thromboembolic complications or early re-occlusion [14, 15]. Overall, up to half of AIS patients still fail to achieve effective vascular reperfusion even after receiving rt-PA and arterial interventional therapy [16-18]. The reperfusion of occluded vessels and their downstream microcirculation is a very important factor in determining the clinical prognosis of AIS patients [19]. Therefore, it is particularly important to seek effective and safe therapy combined with rt-PA or arterial intervention for AIS patients.

## **2. The pathophysiological mechanism of thrombosis and antiplatelet drugs**

Thrombosis is one of the key pathophysiological mechanisms of AIS, and platelet activation plays a central role in the process of arterial thrombosis. Thrombosis requires three elements: vascular endothelial cell injury, changes in blood flow, and increased blood coagulation. Exposure of Von Willebrand factor (VWF), a subendothelial matrix protein, and collagen occurs after rupture of atherosclerotic plaques, interventional therapy, or other causes of vascular endothelial cell injury [20]. VWF binds to naked collagen and unfolds it, exposing multiple binding sites of platelet glycoproteins (GPIb-IX-V). Under arterial shear stress, GPIb interacts with VWF to mediate the transient

adhesion of platelets [21], enabling GPVI on the surface of platelets to combine with collagen to achieve stable adhesion of platelets [22, 23]. Collagen binding to GPVI can lead to platelet activation and the release of soluble agonists adenosine diphosphate (ADP), thromboxane A2 (TXA2) and thrombin. The released ADP, TXA2 and thrombin can act on P2Y purine receptors 1 and 12 (P2Y1 and P2Y12) in addition to directly activating platelets [24-27].

Figure 1 Mechanism of platelet adhesion and aggregation [31] (Due to the copyright issue please find the figure on the page 2 in reference 31)

Activated platelets cause conformational changes of GP IIb/IIIa through "inward outward" signaling, which changes them from a low-affinity state at rest to a high-affinity state. Activated GPIIb/IIIa can bind soluble plasma proteins, including VWF, fibronectin and its main ligand fibrinogen, and promote stable platelet aggregation and thrombosis [28, 29]. The production of thrombin enhances the activation of platelets and activates the coagulation process, enabling the formation of a stable fibrin mesh [30] (Figure 1). Therefore, moderation of platelet activation pathways is a key focus of AIS prevention and treatment.

At present, four classes of antiplatelet drugs are mainly used in clinics (Figure 2): ① cyclooxygenase 1 (cox1) inhibitors, such as aspirin. Cox1 is the enzyme that catalyzes the generation of TXA2 from arachidonic acid. Aspirin prevents TXA2 production by irreversibly inhibiting cox1, thereby inhibiting TXA2 induced platelet activation and aggregation [32, 33]; ② P2Y12 receptor inhibitors such as cangrelor, clopidogrel, prasugrel and ticagrelor. The P2Y12 receptor plays an important role in mediating the sustained activation of GPIIb/IIIa, the major platelet adhesion receptor, in response to ADP stimulation. P2Y12 receptor antagonists inhibit ADP induced enhancement of platelet activation, thereby producing potent antithrombotic effects [34]. However, up to 10% of patients on dual antiplatelet therapy with aspirin and clopidogrel still experience recurrent ischemic events within 12 months. In addition, platelet reactivity

continues to increase in 30-40% of patients treated with clopidogrel [35]. The existence of these problems has inspired people to develop new antiplatelet drugs; ③ Protease activated receptor 1 (PAR1) antagonist, such as vorapaxar. Thrombin is the most potent platelet agonist. PAR1 antagonists target thrombin, thereby exerting antithrombotic effects [36]. However, several studies have shown that vorapaxar significantly increases the rate of intracranial hemorrhage in patients with ischemic stroke [37], limiting its application in clinical practice. This drug is currently contraindicated for patients with a history of stroke, transient ischemic attack or intracranial hemorrhage; ④ GPIIb / IIIa receptor antagonists (GPI), such as abciximab, tirofiban and eptifibatide. GPIIb/IIIa receptor antagonists target the final pathway of platelet aggregation by competing with fibrinogen and vWF for binding to GPIIb/IIIa receptors [38]. One additional antiplatelet drug that inhibits phosphodiesterase, cilostazol, is currently only approved by the US Food and Drug Administration (FDA) for the treatment of peripheral vascular disease.

### **3. Study status of tirofiban for endovascular treatment in acute ischemic stroke**

Tirofiban is the main GPIIb/IIIa receptor antagonist used in China. Tirofiban, which was approved in China in 2004, has the characteristics of strong specificity, high, though dose-dependent potency, and reversibility [39]. It can act on the final pathway of platelet aggregation, effectively preventing platelet mediated thrombosis and vessel re-occlusion. The safety and efficacy of tirofiban in the treatment of patients with acute coronary syndrome (ACS) have been extensively confirmed, and it has been widely used in clinical practice [40-49].

Figure 2 Diagram of antiplatelet therapeutic targets [31] (Due to the copyright issue please find the figure on the page 4 in reference 31)

In recent years, the application of tirofiban in AIS has attracted much attention.

Investigators and clinicians from different countries are focused on the application of tirofiban and have conducted a series of clinical trials to explore the effectiveness and safety of tirofiban in preventing early arterial re-occlusion and thromboembolic complications in AIS [50-74]. However, due to the limited sample size of most studies and the heterogeneity of treatment protocols and dosage regimens, the results of the studies thus far are contradictory and inconclusive. A consensus on the safety and efficacy profiles of tirofiban in AIS has not yet been achieved from the meta-analysis and systematic review based on these clinical trials. Several studies including meta-analysis [14, 64] have concluded that the combined application of tirofiban and endovascular treatment (EVT) of ischaemic stroke will increase the risk of intracranial hemorrhage (ICH). A prospective cohort study in 2013, which enrolled 191 consecutive patients who underwent EVT from 2006 to 2011 concluded that the use of tirofiban was associated with an increased risk of fatal ICH and a poor prognosis [14]. Moreover, a cohort study from Wu showed that the bleeding risk of tirofiban in EVT is dose-dependent [64]. However, several other meta-analyses have reached the opposite conclusion. Guo et al [75] found that early use of tirofiban treatment did not increase the risk of any ICH and death in AIS patients receiving EVT, but there was no association between tirofiban treatment and functional outcome or recanalization rate, suggesting that tirofiban treatment may be safe for AIS patients, but further study is needed to test its efficacy. Meanwhile, the study of Zhou et al [76] found that tirofiban treatment may be safe for AIS patients receiving intravenous thrombolysis, but its effect on improving functional outcomes is unclear. A recent meta-analysis [77] suggested that tirofiban treatment significantly increased the incidence of good functional outcomes and did not increase the risk and mortality or symptomatic intracranial hemorrhage in the Chinese population. This analysis included more recently published studies. In conclusion, those studies including the latest meta-analysis and review are limited and the sample sizes were small. Most of the included studies are observational studies rather than randomized controlled trials (RCTs), which may affect the results due to the related inherent risk of bias. At present, it is impossible to draw a conclusion on the efficacy of tirofiban for AIS patients receiving EVT. Therefore, a high-quality

multicenter randomized controlled trial with a large sample size is needed to provide reliable clinical evidence on the safety and efficacy of tirofiban in AIS.

#### **4. Summary**

Based on the efficient dose-dependent inhibitory effect of tirofiban on platelet aggregation [78] and conflicting conclusions from previous studies applying different routes of administration (particularly by intravenous and intra-arterial pathways) [51, 60, 64], it is hypothesized that therapy regimens of tirofiban (including the route of administration and medication dosage) perhaps account for the variation in clinical benefits and bleeding risks during EVT. We reviewed the studies on tirofiban dosage during endovascular treatment of acute large-artery occlusive stroke. Yang et al. [51] showed that when a large dose of 10  $\mu\text{g} / \text{kg}$  of tirofiban was injected intra-arterially or intravenously, and then intravenously at a speed of 0.15  $\mu\text{g} / (\text{kg} \cdot \text{min})$  for 12-24 hours as an adjunct to EVT, intravenous tirofiban had a high recanalization rate and good prognosis, while intraarterial tirofiban has higher bleeding rate and mortality. Pan, Torgano, Gruber, et al [58, 62, 73] applied the same or greater dose of tirofiban intravenously, and the results suggested that the risk of intracranial hemorrhage and death was not increased. The safety of this dose of tirofiban in AIS patients was supported. According to the recommended usage of tirofiban in the instruction manual of angioplasty / intra-arterial atherectomy in ACS patients, we preliminarily concluded that for some patients, tirofiban 10  $\mu\text{g}/\text{kg}$  intravenous bolus injection and 0.15 $\mu\text{g}/(\text{kg} \cdot \text{min})$  intravenous infusion for 12-24 hours is clinically feasible. Therefore, we designed this prospective, randomized, controlled, open-label, multicenter clinical study and selected this dose of tirofiban to evaluate the safety and efficacy of tirofiban in combination with EVT in AIS patients and provide more basis for clinical study and clinical application.

#### **V. Study objective**

## **1. Primary objective**

To determine, for acute ischemic stroke patients treated with thrombectomy, whether intravenous tirofiban treatment can increase the probability of first-pass recanalization of targeted vessels without increasing the risk of symptomatic intracranial hemorrhage.

## **2. Secondary objectives**

To determine whether intravenous tirofiban combined with thrombectomy, compared to thrombectomy alone, has affects the following outcomes: the recanalization rate of targeted vessels after thrombectomy, the recanalization rate of targeted vessels at the end of endovascular treatment, the recanalization rate of targeted vessels at 24-72 hours, symptomatic intracranial hemorrhage, and 90-day functional outcomes(dichotomized 90-day mRS, ordinal scale of 90-day mRS); death at 90 days; number of thrombectomy passes.

## **VI. Methods**

### **1. Overall design**

This study is a multicenter, prospective, randomized, controlled, open-label, blinded-endpoint study. A total of 200 patients with acute ischemic stroke who are scheduled to undergo thrombectomy will be recruited from 10-15 hospitals in China. They will be randomly assigned 1:1 to the study group or control group. The study design is shown by the following study schema (study design flow chart).

## 2. Study schema (flow chart)

[figure not shown]

## 3. Study population

All patients with acute ischemic stroke who are going to undergo thrombectomy in the

sites participating in the trial will be considered for study enrollment. The principal investigator of each site takes the primary responsibility for patient enrollment. As it is necessary to enroll stroke patients before receiving thrombectomy, it is expected that successful enrollment will require the active participation of relevant physicians at each site. The following factors are expected to limit the enrollment speed:

- (1) The absolute number of thrombectomy cases performed.
- (2) Compliance with inclusion and exclusion criteria.
- (3) Informed consent obtained and baseline evaluation.

#### **4. Inclusion and exclusion criteria**

To meet the enrollment criteria of this study, patients must meet the local routine criteria for thrombectomy, and the attending physician should consider the clinical uncertainty of each patient and weigh the possible benefits and risks of tirofiban treatment. In addition to routine site selection for thrombectomy, patients must meet the following study criteria:

##### ***4.1 Inclusion criteria***

- [1] Age 18-85 years (inclusive);
- [2] Acute ischemic stroke within 24 hours of onset, and NIHSS >5.
- [3] Acute large vessel occlusion, such as internal carotid artery, M1 or M2 segment of middle cerebral artery.
- [4] Multimodal CT/MRI imaging completed before thrombectomy, demonstrating penumbra>10ml, infarct core volume <70ml, and mismatch rate >1.2;
- [5] Planned to receive endovascular treatment
- [6] Informed consent was obtained.

##### ***4.2 Exclusion criteria***

- [1] History of atrial fibrillation or atrial flutter, or 12-lead ECG before randomization and after admission showing atrial flutter or atrial fibrillation.
- [2] Treated with intravenous thrombolysis for this stroke or currently taking new oral anticoagulant drugs, warfarin, ticagrelor, and other drugs that may increase the risk of bleeding.
- [3] Pre-stroke disability (pre-stroke mRS score > 2).
- [4] Severe comorbidity (such as severe cardiopulmonary dysfunction, or the terminal stage of malignant tumors with expected survival less than 90 days).
- [5] CT shows hypodensity lesions in more than 1 / 3 of the territory of the middle cerebral artery.
- [6] Allergy to tirofiban or having any contraindications to the use of tirofiban (patients with active internal bleeding, history of intracranial hemorrhage, intracranial tumors, arteriovenous malformations, and intracranial aneurysms, or patients resulting in thrombocytopenia from the use of tirofiban previously).
- [7] Contraindications to the contrast agents used in multimodal CT/MRI examination (such as allergy to the contrast agents, etc.).
- [8] Pregnant or breastfeeding women.
- [9] Patients currently participating in other clinical trials.
- [10] Other conditions determined by the investigator are not suitable for inclusion in this study.

## **5. Ethical issues**

This study follows the principles stated in the Helsinki Declaration of the World Medical Association.

### ***5.1 Institutional ethics committee approval***

Each participating site must obtain written approval(s) from their Institutional Research Ethics Committee (e.g. Institutional Review Board [IRB]) before patient recruitment can commence. Any protocol amendments, serious adverse events (SAEs) reports and routine reporting to the IRB will be the responsibility of the Principal Investigator (PI) at each participating center.

## ***5.2 Informed consent***

Most patients with acute large artery ischemic stroke require emergency treatment, including thrombectomy. However, the acute characteristics of this disease mean that patients may not be able understand the study and provide informed consent before emergency treatment. The optional informed consent steps in this study are detailed below, and any local ethics committee requirements should be followed.

### **5.2.1 Patient informed consent**

Whenever possible, written informed consent should be obtained. Clinicians familiar with the study protocol should explain the study to patients and obtain consent to participate in this study.

### **5.2.2 Surrogate informed consent**

If the patient is not fully competent for the consent, for example, because of a reduced level of consciousness, the patient's "surrogate" will be approached to provide informed consent on behalf of the patient.

### **5.2.3 Withdrawal of consent**

The information forms provided to patients and / or their surrogates clearly show that patients can withdraw from the study at any time without explanation, and patients will not be discriminated against or impaired. This situation should be recorded in the patient file. If the patient's withdrawal of consent is only to discontinue tirofiban

medication, further data can be collected and recorded.

#### **5.2.4 Confidentiality and privacy**

Patients' privacy should be respected in the conduct of the study. The submitted data will be de-identified to maintain the confidentiality of participants. However, where necessary in the process of monitoring data quality and adherence to the study protocol, the monitors may review medical records at participating hospitals.

### **6 Randomization**

#### ***6.1 Randomization procedure***

Patients who meet the inclusion criteria are assigned 1:1 to the study group and control group according to the permuted-block randomization method to ensure the balance between and within the groups. Randomization is stratified by participating sites.

#### **Procedures for patients with incorrect inclusion or randomization**

If a patient who does not meet the inclusion/exclusion criteria is enrolled in this study, the following procedures should be followed:

- 1) The investigator or monitors shall immediately notify the physician of the study team to ensure the safety of patients as the primary focus.
- 2) If continuing the study treatment may endanger the safety of patients, the study treatment must be stopped. After discussion between the study team physician and the investigator, the decision will be made whether to discontinue the study drug. The reasons for discontinuing study treatment must be clearly documented. Patients should be followed up according to the specified study process, including the follow-up of endpoint events until the end of the study, in accordance with the intention-to-treat principle.
- 3) If continuation of the study is considered not to pose a risk to the patient, nor affect

the treatment of the disease, the reasons for continuing the study should be clearly recorded. Patients should continue to receive follow-up according to the planned study process.

## ***6.2 Blinded follow-up***

The follow-up images are uploaded to the local server by each center or the leading center, and the leading center will arrange analysis by trained analysts blinded to treatment group information, including two analysts specialized in neuro-intervention for vascular recanalization, and two analysts mainly engaged in neuroimaging for bleeding analysis.

The clinical evaluation on 90-day follow-up will be performed by a trained professional in the leading center who has no access to the treatment group information of patients.

## ***6.3 Blinded review***

After the blinded review and confirmation of the accuracy of the established database, the principal investigator and statistical analyst will lock the data. The locked data is not subject to any change.

# **7 Interventions**

## ***7.1 Study drug***

### **7.1.1 Tirofiban drug selection**

Drug name: Tirofiban hydrochloride sodium chloride injection

Drug specifications: 100ml: tirofiban hydrochloride 5mg

#### **7.1.2 Drug label:**

|                 |  |
|-----------------|--|
| Patient number: |  |
|-----------------|--|

|                   |  |
|-------------------|--|
| Patient initials: |  |
| Date of use:      |  |
| Product No.:      |  |

## ***7.2 Drug dosage and regimen***

**The study group:** intravenous tirofiban combined with thrombectomy. Tirofiban intravenous therapy is initiated within half an hour after randomization and before femoral artery puncture. Tirofiban is used as follows: tirofiban 10 µg/kg, intravenous bolus injection within 3 minutes, and 0.1 µg/kg/min intravenous infusion for 24 hours. The study group is required to maintain tirofiban medication for at least 24 hours according to the protocol. If intracranial hemorrhage is found in follow-up head CT or other serious adverse events (such as gastrointestinal or urinary tract hemorrhage) that may be related to tirofiban within 24 hours, the investigator may consider stopping the medication. The site investigators decide on the subsequent antiplatelet treatment plan based on the patient's condition after 24 hours of intravenous tirofiban infusion.

**The control group:** treated with routine thrombectomy. The control group is not allowed to use intravenous or intraarterial antiplatelet drugs before the first thrombectomy attempt. Other thrombectomy procedures are carried out in accordance with local guidelines. If there is obvious vascular stenosis or re-occlusion after thrombectomy, the operator can use other rescue measures according to the circumstances, including intra-arterial tirofiban treatment. The rescue treatment does not include an intravenous loading dose of tirofiban.

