## ***7.4 Procedural method***

It is recommended that the time from randomization to femoral artery puncture should be ≤ 90 minutes. During the procedure, all participants are required to undergo a first

thrombectomy attempt after cerebral angiography evaluation. After the first pass thrombectomy, the operator can determine the remaining procedural plan according to the procedural situation. The operator can use other rescue measures at his/her discretion, including balloon dilatation and/or stenting. The control group could use arterial tirofiban rescue treatment after the first pass of thrombectomy, while intra-arterial tirofiban treatment is not recommended for the study group.

Heparinization during the procedure is prohibited.

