### ***10.4 Treatment information (0-24h)***

- Tirofiban administration information, including tirofiban intravenous bolus start time, intravenous bolus dose, intravenous infusion start time, and intravenous infusion end time. Ensure that the patient treatment complies with their randomization.
- Endovascular treatment information, including the mTICI grade of targeted vessels after the first angiography, mTICI grade of targeted vessels after the first-

pass thrombectomy, thrombectomy devices (second-generation, third-generation, aspiration or other), degree of stenosis after thrombectomy, number of thrombectomy passes, mTICI grade of targeted vessels after thrombectomy, use or otherwise of balloon dilatation or stent implantation, the final mTICI grade at the end of endovascular thrombectomy, and the final residual stenosis (0-30%; 30-50%; 50-70%, 70-99%). Intraoperative complications, femoral artery puncture time, DSA first angiography time, final recanalization time.

- Brain imaging: DSA collected the endovascular treatment process.
- Concomitant medication: antiplatelet drugs (aspirin, clopidogrel, cilostazol, others); Anticoagulant drugs.

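### The secondary objectives name thrombectomy alone as the comparator, but controls may receive intra-arterial tirofiban rescue after the first pass, so the bleeding, late recanalization, death and mRS comparisons are mislabelled

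*Protocol*

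**What the plan says.** **Objective.** Protocol V.2, like the Synopsis, sets the secondary comparison as "intravenous tirofiban combined with thrombectomy, compared to thrombectomy alone". It covers recanalization after thrombectomy, at the end of treatment and at 24-72 hours, sICH, 90-day mRS, 90-day death and number of passes.

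**Control arm.** Section 7.2 sets one restriction before the first pass: "The control group is not allowed to use intravenous or intraarterial antiplatelet drugs before the first thrombectomy attempt". After that it says that, for obvious stenosis or re-occlusion, "the operator can use other rescue measures according to the circumstances, including intra-arterial tirofiban treatment". It adds one limit: "The rescue treatment does not include an intravenous loading dose of tirofiban". Section 7.4 says "The control group could use arterial tirofiban rescue treatment after the first pass of thrombectomy" and does not recommend intra-arterial tirofiban for the study group.

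**Outcomes.** Section 9 grades first-pass recanalization before stenting, balloon dilation or platelet therapy. sICH is a secondary outcome within 72 hours, and its absence also forms part of the composite primary outcome.

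**Background.** IV.4 (Summary) reports a favourable result for the IV route in one cited study, "while intraarterial tirofiban has higher bleeding rate and mortality".

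**Data.** Section 10.4 asks for "Tirofiban administration information, including tirofiban intravenous bolus start time, intravenous bolus dose, intravenous infusion start time, and intravenous infusion end time". Balloon dilatation and stenting have their own entries. Intra-arterial tirofiban has none, and could appear only under a general line for antiplatelet drugs that ends in a catch-all.

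**The concern.** The comparator in the objectives is not the control arm described in the interventions section. Controls are kept free of antiplatelet drugs only up to the first attempt. From then on they may receive the drug under test by another route, in an open-label trial in which access to that route differs by arm.

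Bleeding is where this matters most. The primary objective asks for more first-pass recanalization without more sICH, and sICH is observed after any rescue has been given. If the sICH rates come out alike, a report that follows the stated objective would conclude that IV tirofiban adds no bleeding to thrombectomy alone. The design cannot show that, because some controls may themselves have been exposed to tirofiban. End-of-treatment and 24-72 hour recanalization, death and mRS have the same difficulty. If the route, dose, timing and reason for rescue are not recorded as they happen, the extent of the exposure cannot be reliably recovered later.

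**Working it through.** **1. Which outcomes can follow rescue in a control**

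| Outcome | When read | After possible rescue? |
|---|---|---|
| First-pass recanalization | Before platelet therapy (section 9) | No |
| Recanalization at end of treatment | End of procedure | Yes |
| Recanalization at 24-72 h | Follow-up imaging | Yes |
| sICH | Within 72 h | Yes |
| Death, mRS | 90 days | Yes |

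Recanalization after thrombectomy and the number of passes may or may not follow rescue, depending on when it is given. They are not counted here.

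**2. The plan's own figure.** Inputs from XI.4: 50% versus 70%, two-sided alpha 0.05, power 80%, dropout 7%. With the pooled-variance formula and mean rate 0.60:

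n = [1.96 × √(2 × 0.60 × 0.40) + 0.8416 × √(0.50 × 0.50 + 0.70 × 0.30)]² / 0.20² = (1.358 + 0.571)² / 0.04 ≈ 93 per arm.

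93 / 0.93 = 100 per arm, 200 in total. The stated size reproduces, and rescue does not alter it.

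**3. Effect of rescue on an sICH difference.** Let p0 be the sICH rate without tirofiban, e the excess from IV tirofiban, r the share of controls given rescue tirofiban, and k the ratio of the rescue excess to the IV excess.

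- Study arm: p0 + e
- Control arm: p0 + r·k·e
- Observed difference: (1 − r·k)·e

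The protocol gives none of p0, e, r or k, so all values below are assumptions. With p0 = 5%, e = 5 points and k = 1:

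| r | Control sICH | Study sICH | Difference | Risk ratio | Power, 100 per arm |
|---|---|---|---|---|---|
| 0 | 5.0% | 10% | 5.0 points | 2.00 | 27% |
| 20% | 6.0% | 10% | 4.0 points | 1.67 | 18% |
| 30% | 6.5% | 10% | 3.5 points | 1.54 | 14% |
| 50% | 7.5% | 10% | 2.5 points | 1.33 | 9% |

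With k = 2 and r = 50%, the difference is (1 − 0.5 × 2) × 5 = 0.

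**4. How much of the weakness on sICH is due to rescue.** Over p0 = 3%, 5% and 8% and e = 3 and 5 points, power at 100 per arm is 11% to 34% with no rescue, and 5% to 10% with half of controls rescued. Sample size is the main limit; rescue adds to it.

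**5. Effect on the composite primary outcome.** Rescue matters only if a control with first-pass success is then given tirofiban and bleeds. Taking 50% as the approximate share of controls with first-pass success, with equal excess risk and r now the share rescued among them, the fall in control success is 0.50 × r × e:

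- smallest case: 0.50 × 10% × 3 points = 0.15 points
- largest case: 0.50 × 50% × 5 points = 1.25 points

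The shift is small and favours the study arm.

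**The case against.** The strongest reply is that the control strategy is disclosed. Sections 7.2 and 7.4 state it openly, and XI.4 calls the control arm routine thrombectomy. Discretionary rescue is an ordinary pragmatic choice, and the first-pass outcome is deliberately protected from it. The primary objective itself never names thrombectomy alone. All of this stands, and it rules out several stronger readings that a reader might infer:

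- **That no valid comparison remains for the later outcomes.** Rescue is optional, and the as-randomized contrast is sound for early IV tirofiban against thrombectomy with rescue permitted. Only the label and the inference drawn from it are wrong.
- **That about half of controls are rescue candidates, from the 50% in XI.4.** That figure is a composite success rate, and section 7.2 ties rescue to stenosis or re-occlusion. A failed first pass may simply lead to another pass, and a successful one may leave a stenosis. The figure does not bound rescue use in either direction.
- **That the background shows rescue will raise control bleeding by a known amount.** IV.4 gives no rates. In the study it cites, the bolus was followed by an IV infusion, a regimen that sections 7.2 and 7.4 do not specify for rescue.
- **That section 7.4 allows rescue at any moment, against 7.2.** It says only after the first pass. The two can be read together as indication and earliest timing, although the text does not say so.
- **That rescue cannot be captured at all.** The list in 10.4 is not exhaustive, the flow chart schedules tirofiban and concomitant medication without limiting them to one arm, and the case report form is not at hand. What can be said is that 10.4 names only IV tirofiban items.

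None of this removes the mismatch between the objectives and the interventions section.

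**Conclusion.** The concern holds as a wrong comparator label with a consequence for inference. For end-of-treatment and 24-72 hour recanalization, sICH within 72 hours, and 90-day death and mRS, the trial compares early IV tirofiban with thrombectomy plus optional tirofiban rescue. A similar sICH rate therefore cannot be read as no added bleeding over thrombectomy alone. First-pass recanalization and the sample size are unaffected.

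The direction of dilution follows if rescue carries some excess bleeding risk. At equal excess risk the sICH difference shrinks by exactly the share of controls rescued. The size is unknown, because the protocol gives neither a rescue rate nor an sICH rate. A reader might infer that a null sICH result would be caused mainly by rescue. The calculations do not support that: power on sICH is low at 100 per arm with no rescue at all.

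**What to change.** 1. In V.2 and the Synopsis, name the comparator as routine thrombectomy with tirofiban rescue permitted after the first pass. Limit the sICH, death and mRS conclusions to that comparison.
2. In section 10.4, add an item for rescue tirofiban in either arm: route, dose, time and indication. Report rescue use by arm, and sICH by tirofiban exposure as descriptive support only. Rescue is selected after randomization and sICH events will be few, so a weighted adjustment for rescue would be fragile.
3. Reconcile the rescue wording of sections 7.2 and 7.4, and state whether an IV tirofiban infusion in a control falls within rescue. Section 7.2 excludes only the IV loading dose, and section 7.5 addresses only other IV platelet inhibitors. Which clinical rule applies is for the investigators to state.

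The cost is wording in two objective paragraphs, one extra block in the case report form and a narrower stated conclusion. Enrolment and sample size do not change.
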